## 9.7 Warnings and Precautions

The risks of treatment with Opal-HIV-Gag(c) not been evaluated and the risks are unknown. For information regarding precautions and AEs with the IMP, the Investigator is referred to the IB for Opal-HIV-Gag(c).

## 9.8 Risks for Women of Childbearing Potential or during Pregnancy

The risks of treatment with Opal-HIV-Gag(c) during pregnancy have not been evaluated. Pre-menopausal women of childbearing potential will follow a medically prescribed birth control regimen using two methods of contraception or agree to abstain from heterosexual intercourse while participating in the study and for 30 days following the last dose of study product.

## 9.9 Procedures to be followed in the Event of Pregnancy

The subject must be instructed to inform the Investigator IMMEDIATELY if she becomes pregnant during the study, and seek advice regarding discontinuation of study medication. Whenever possible, treatment should be discontinued. The Investigator should report all pregnancies to the Sponsor within 24 hours of becoming aware of the pregnancy. Pregnancies should be reported using the form in the CRF for reporting the occurrence and outcome of pregnancies in subjects enrolled in the study.

Prior to discontinuing therapy, the Investigator should counsel the subject and discuss the risks of continuing study product dosing and the possible effects on the fetus.

Monitoring of the subject should continue until conclusion of the pregnancy. The outcome of the pregnancy should be reported to the Sponsor regardless of whether the study is still in progress or not.

## 10 DATA SAFETY MONITORING BOARD REVIEW

The Sponsor has convened a DSMB that is charged with the review of this study. The DSMB review will occur as soon as practical after the W4 dose administration of IMP is complete for each cohort and will include all available safety data.

Each DSMB meeting will have an open session and an optional closed session. Open session review materials will be blinded and include aggregate data on study accrual, baseline characteristics and general study progress, and will be made available to the DSMB, Sponsor representatives, and invited guests (e.g. participating Investigators) to facilitate a general discussion of study progress. Attendance at the closed session will be restricted to DSMB members and those individuals who were directly involved in the preparation of the review materials. The DSMB will review available safety results of the trial and logistical issues such as accrual, retention, quality of clinical and laboratory data, and safety and implications of results of external studies. Unblinding envelopes will be made available to the DSMB should unblinding be requested.

The DSMB will make its recommendation to the Sponsor about dose escalation, halting or termination of the clinical trial. At each meeting the DSMB will review all available safety data and the DSMB will recommend to the Sponsor to:

- proceed with dose escalation
- pause enrolment pending either resolution of specific issues or amendment of the protocol as specified
- pause enrolment and all scheduled trial administrations pending either resolution of specific issues or amendment of the protocol as specified
- terminate the study

The DSMB, following a meeting to review the data, may recommend to the Sponsor and Principal Investigator not to permit further dose escalation if any of the following conditions are met:

- a subject experiences a SAE regarded as “probably” or “definitely” related to Opal-HIV-Gag(c) (i.e unblinded review of the event)
- any three subjects experience a similar severe adverse event (with a toxicity of at least grade 3) which is “probably” or “definitely” related to Opal-HIV-Gag(c) (i.e. unblinded review of the events)
- the Principal Investigator, DSMB and/or the Sponsor feel that consideration by the DSMB of a full interim safety summary is warranted following detection of a pattern of repeated or unresolved clinical AEs or laboratory abnormalities.

The clinical trial will be halted by the Principal Investigator and/or Sponsor for review and recommendation by the DSMB if:

- any three subjects experience a similar severe adverse event (with a toxicity of at least grade 3) which, in the opinion of the Principal Investigator, cannot be attributed to causes other than the IMP. (Note: transient and self-limiting events ‘expected’ in response to receipt of vaccines [such as fever] may not result in halting).
- any subject experiences a serious or severe adverse event, which, in the opinion of the Principal Investigator, contraindicates further dosing of additional subjects.

Refer to the DSMB Charter for further details of the review process.

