## **9.6 Guidance for toxicity management**

AEs and abnormal laboratory values will be graded according to the Toxicity Grading Scale (Appendix A). IMP will be interrupted or discontinued due to toxicity according to the toxicity grading scale.

All abnormal values should be confirmed by repeat testing within 3 calendar days of receipt of results prior to dose adjustment or interruption, unless such a delay is not consistent with good medical practice. For the purpose of monitoring toxicities, the baseline value is defined as the last value prior to the administration of the first dose of study medication. The value must be obtained from the central laboratory. All assessments of toxicity will be based on changes from this value, regardless of later interruptions to dose.

The following table (Table 5) outlines the procedure for temporary or permanent IMP discontinuation due to an AE or SAE. All subjects who experience a study product related AE should be followed until resolution of the AE, even if the subject has interrupted or discontinued study product.

Table 5: Toxicity management.

| Clinical or laboratory* abnormality                                | Action Taken                                     |                                                                                           |
|--------------------------------------------------------------------|--------------------------------------------------|-------------------------------------------------------------------------------------------|
|                                                                    | Continue dosing at Investigator discretion       | Permanently discontinue dosing                                                            |
| Grade 1                                                            | Regardless of causality                          | N/A                                                                                       |
| Grade 2                                                            | Regardless of causality                          | N/A                                                                                       |
| Grade 3
Lab events of clinical significance*
Clinical Events | Unrelated to treatment
Unrelated to treatment | Unknown or at least possibly related
Unknown or at least possibly related # |

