| Grade 4
Lab events of clinical significance*
Clinical Events | Unrelated to treatment
Unrelated to treatment | Unknown or at least possibly related
Unknown or at least possibly related              |

\* All grade 3 or 4 laboratory abnormalities must be confirmed by repeat testing as soon as possible, preferably within 24 hours of receipt of results prior to dose interruption or discontinuation, unless such a delay is not consistent with good medical practice.

#The Investigator may continue dosing at their discretion for transient and self limiting events that may be attributed to IMP but are expected for a vaccine (such as fever): these grade 3 event(s) must be followed to resolution ( $\leq$  grade 2) before the subject is discharged from the clinic.

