|------------------------------------------------------------------------------------------------------------------------------------------------------------------------|----------------------------------------------------------------------------------------|----------------------------------------------------------------------------------------------------------------------|----------------------------------------------------------------------------------------------------------------|--------------------------------------------------------------------------------------------------------------------------------------------------------------------------------------|
| Parameter                                                                                                                                                              | Grade 1
Mild                                                                        | Grade 2
Moderate                                                                                                  | Grade 3
Severe                                                                                              | Grade 4
Potentially life-threatening                                                                                                                                              |
| Clinical AE NOT identified elsewhere in this DAIDS AE grading table                                                                                                    | Symptoms causing no or minimal interference with usual social & functional activities* | Symptoms causing greater than minimal interference with usual social & functional activities                         | Symptoms causing inability to perform usual social & functional activities                                     | Symptoms causing inability to perform basic self-care functions**
OR medical or operative intervention indicated to prevent permanent impairment, persistent disability, or death |

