| Table 5                                                                                                                                                 | Addition of new text                                                                                                                                                                                                                                  | # The Investigator may continue dosing at their discretion for transient and self limiting events that may be attributed to IMP but are expected for a vaccine (such as fever) : these grade 3 event(s) must be followed to resolution ( $\leq$ grade 2) before the subject is discharged from the clinic.                                         | Text added for the clarification of transient and self limiting clinical events expected for a vaccine. |
| 10 Data Safety Monitoring Board Review
5 th Paragraph                                                                                     | Addition of note to existing text:
any three subjects experience a similar severe adverse event (with a toxicity of at least grade 3) which, which in the opinion of the Principal Investigator, cannot be attributed to causes other than the IMP | any three subjects experience a similar severe adverse event (with a toxicity of at least grade 3) which, which in the opinion of the Principal Investigator, cannot be attributed to causes other than the IMP (Note: transient and self limiting events ‘expected’ in response to receipt of vaccines (such as fever) may not result in halting. | Text added for the clarification of transient and self limiting clinical events expected for a vaccine. |

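### The Section 10 halting note exempts transient expected vaccine events with no grade limit, so three Grade 4 fevers attributed to the IMP would not require a halt (minor, cheap to fix)

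*Protocol*

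**What the plan says.** Section 10 gives two conditions under which the Principal Investigator and/or the Sponsor halt the trial for DSMB review. The first is a count: three subjects with a similar event of grade 3 or higher which, in the Principal Investigator's opinion, has no cause other than the IMP. The note attached to it says that transient, self-limiting events expected "in response to receipt of vaccines [such as fever] may not result in halting". The second is any single serious or severe event that the Principal Investigator believes rules out dosing more subjects.

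Section 9.6, Table 5, governs the individual subject. Under the heading "Permanently discontinue dosing" it places Grade 3 and Grade 4 clinical events whose relation to treatment is unknown or at least possible. A footnote lets the Investigator continue dosing for "transient and self limiting events that may be attributed to IMP but are expected for a vaccine (such as fever): these grade 3 event(s" and requires these events to settle to grade 2 or lower before discharge. The footnote marker sits on the Grade 3 clinical-event cell only; the Grade 4 row has none.

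Appendix D (Amendment 2) gives one rationale for both notes: "Text added for the clarification of transient and self limiting clinical events expected for a vaccine".

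Appendix A grades non-axillary fever as 3 from 39.4 to 40.5°C and as 4 above 40.5°C. Its Grade 4 column is headed "Potentially life-threatening".

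**The concern.** A count-based halting rule exists to take the decision out of individual judgement once a set threshold is reached. This is the only such rule in the protocol. It is triggered at grade 3 or higher, so it includes Grade 4, but the note then hands part of it back to judgement without saying how severe an exempted event may be. The word expected is not defined there, and Section 2.4 says the product has never been given to humans, so no human experience with it limits what may be called expected.

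The drafters saw the need for a limit in Table 5 and wrote one. In Section 10, where the consequence is for the whole trial, they did not. What is at stake is whether three IMP-attributed fevers above 40.5°C in a first-in-human infusion study must stop dosing until the DSMB has looked, or only may.

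**Working it through.** The point is settled by the text; the arithmetic only describes the schedule around it.

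**1. The two notes side by side**

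| | Section 10 note | Table 5 footnote |
|---|---|---|
| What it governs | Halting the whole trial | Dosing of one subject |
| Events covered | Transient, self-limiting, expected for a vaccine; fever as example | Same description, same example |
| Grade limit | None stated; the rule it qualifies starts at grade 3 | Grade 3 clinical events only |
| Grade 4 event | May be exempted | Not exempted: dosing stops if relation is unknown or at least possible |
| Force | Permissive | Permissive |

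**2. Can the note's example reach Grade 4?** Yes, on temperature alone (above 40.5°C, Appendix A). Such a fever can be short and resolve by itself, so the words transient and self-limiting do not act as a grade limit.

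**3. Does another provision make a halt mandatory for three such fevers?**

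- The second halting condition depends on the Principal Investigator's opinion.
- The DSMB criterion "any three subjects experience a similar severe adverse event (with a toxicity of at least grade 3) which is" probably or definitely related has no exemption, but the DSMB only may act on it, and it concerns escalation. The same holds for the single related SAE criterion.
- The review of a full safety summary where it is felt to be "warranted following detection of a pattern of repeated or unresolved clinical AEs or laboratory abnormalities" is also discretionary.
- SAEs are reported within 24 hours (Section 9.3.2.1), but Section 9.3.1 reserves life-threatening for immediate risk of death. A temperature reading does not establish that by itself.
- The Sponsor, the ethics committee or regulators may terminate the study (Section 11.6). None is obliged to on this count.
- Table 5 stops only the affected subjects.

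The answer is no.

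**4. The protocol's own figures nearby.** Section 12.2 gives the chance of three or more related events of grade 3 or higher among 18 active subjects, P(X ≥ 3) = 1 − Σ (k = 0 to 2) C(18, k) p^k (1 − p)^(18 − k). At p = 5%, 10%, 20% and 30% this gives 5.81%, 26.62%, 72.87% and 94.00%, which match the stated 5.8%, 26.6%, 72.9% and 94.0%. They do not bear on the note's grade limit, and the protocol gives no Grade 4 rate from which to compute anything that would.

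**5. The schedule in cohort 3.** Inputs: 6 active subjects at 48 mg and doses at Weeks 0, 4, 8 and 12 (Section 4.2). On timing, Section 10 says: "The DSMB review will occur as soon as practical after the W4 dose administration of IMP is complete for each cohort".

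- Active doses planned: 6 × 4 = 24.
- Active doses at Weeks 8 and 12: 6 × 2 = 12.

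After this review no escalation decision remains, and the protocol names no later DSMB meeting. Some subjects may already have had Week 8 by the time it is held, so fewer than 12 may actually follow it.

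**6. How many doses would follow three Grade 4 fevers?** There is no single figure. If all three were in active cohort 3 subjects, Table 5 would leave (6 − 3) × 2 = 6 of these doses. If the cohort 3 fevers were in placebo recipients, all 6 × 2 = 12 would remain. Both cases are possible because Section 9.2 counts placebo as IMP and Section 7.2 blinds the investigator. These are scenarios, not bounds.

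**The case against.** The strongest case is that nothing here is an error. The note permits continuing; it leaves the Principal Investigator and the Sponsor each free to halt. To be exempt, an event must be transient, self-limiting and expected, and it is doubtful that an investigator would describe three fevers above 40.5°C that way. The shared amendment rationale invites reading the two notes together, with the Grade 3 limit understood. Judgement is built into the rule anyway, since attribution rests on the Principal Investigator's opinion. The DSMB reviews all available safety data, may recommend pausing all administrations, and may have further meetings under a Charter that is not shown. The synopsis also lists treatment-related Grade 3 or 4 toxicity as a bar to further dosing, although this appears to concern the individual subject.

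Most of this stands, and it is why the point is minor. What it does not do is supply the missing limit: a shared rationale is not a stated cap, and every remaining safeguard is either discretionary or acts on single subjects. Judgement about cause is also different from judgement about whether a Grade 4 event counts at all.

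A reader might infer that Section 10 and Table 5 contradict each other. They do not: one concerns the trial and the other a subject, so both can be followed at once. A reader might also infer that the note forbids a halt for fever. Its wording does not say that.

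**Conclusion.** The point holds as a missing grade limit in a stated halting rule. If three subjects had Grade 4 fevers attributed to the IMP and judged transient and expected, Section 10 as written would not require a halt, although it would allow one. Severity is minor, and the change is a cheap improvement.

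The conclusion rests on the current wording of Section 10, Table 5 and Appendix A, and on no assumed event rate. A reader might want a ceiling on how many active doses could follow such a cluster; the documents do not support one, because placebo fevers can count towards the three. The most that can be said is that the 12 active Week 8 and Week 12 doses in cohort 3 are scheduled after the Week 4 dose that prompts the last DSMB review named in the protocol. That late-cohort argument is conditional on the Charter adding no meetings.

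**What to change.** Reword the Section 10 note so that only transient, self-limiting Grade 3 clinical events expected for a vaccine may be exempted, and state that any Grade 4 event meeting the condition counts towards the three-subject halt. This brings the note into line with the limit already in Table 5. Leave the DSMB escalation criterion as it is, without an exemption. If the DSMB Charter repeats the note, change it there too.

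The cost is one sentence in the protocol, possibly one in the Charter, and an occasional extra review by the existing DSMB.

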## **11 SUBJECT COMPLETION / WITHDRAWAL**

### **11.1 Subject Completion**

A subject will be deemed to have completed the study once all trial procedures have been conducted. Any AEs or SAEs still ongoing at the time of the Exit Evaluation will be followed in accordance with Section 9.

### **11.2 Criteria for Premature Withdrawal from Treatment or the Study**

Subjects have the right to withdraw from treatment or the study at any time for any reason. The Investigator must make every reasonable effort to keep each subject in the study except where termination or withdrawal is for reasons of safety. The Investigator also has the right to withdraw patients from treatment or the study in the event of intercurrent illness, AEs, pregnancy, treatment failure after a prescribed procedure, protocol violations, administrative reasons or other reasons.

It is understood by all concerned that an excessive rate of withdrawals from the study can render the study difficult to interpret. In particular, missing data on virological or histological assessments could significantly impact on the interpretation of the results; therefore, unnecessary withdrawal of subjects from the study should be avoided.

The reasons for withdrawal of the subject must be recorded on the CRF. The following are considered justifiable reasons for subject withdrawal:

- the need to take medication which may interfere with study measurements
- intolerable/unacceptable adverse experiences
- major violation or deviation of study protocol
- non-compliance of subject with protocol
- subject unwilling to proceed and/or consent is withdrawn
- withdrawal from the study is, in the Investigator's judgement, in the subject's best interest
- pregnancy of female study subject at any time during the study period (if applicable).

### **11.3 Withdrawal of subjects from Study Product**

Section 9.6 provides guidance for dose modification or discontinuation of IMP in the event of AEs or abnormal laboratory values.

If a subject permanently discontinues dosing with IMP (for example, as a result of an AE), every attempt should be made to keep the subject in the study and continue to perform the required follow-up and procedures. The ideal is to continue to follow the subject for the full study period or until resolution of the AE. If it is not possible for the subject to remain in the study for the full study period, every attempt should be made to keep the subject in the study up to W16. If the subject remains in the study but off study treatment, all study procedures should continue as per protocol or equivalent assessments during the on-study period, such as pre-dosing study assessments at W4, 8 and 12.

If the subject will not remain in the study for all study related procedures, the Exit Evaluation should be performed wherever possible.

All subjects who discontinue IMP dosing should be followed for at least 30 days after the last dose of IMP in order to monitor subjects for possible post-treatment AEs which may occur after IMP has been discontinued.

#### **11.4 Withdrawal of Subjects from the Study**

Should a subject decide to withdraw from the study, all efforts will be made to complete and report the observations as thoroughly as possible.

If the reason for removal of a subject from the study is an AE or an abnormal laboratory test result, the principal reason will also be recorded on the CRF AE page. Where possible, subjects should be followed until the AE is resolved or the abnormal laboratory test has returned to normal.

